## Introduction

### Background

The first law of thermodynamics, also known as the law of conservation of energy, states that energy can neither be created nor destroyed in an isolated system [1]. The human body has its own mechanisms to adapt to changing temperatures; however, it is possible that higher or lower temperatures of food and beverages (referred to as dietary temperature) impose some implications on the energy demands of the body. On the basis of diet composition, chewing habits, and the amount of fluid (and its corresponding temperature) ingested, the human body is exposed to a wide range of temperatures [2,3]. This exposure affects the entire gastrointestinal tract, being greatest at the mouth, followed by the esophagus and stomach, with the latter exposed for a greater time [4-7]. Indeed, there have been several studies relating dietary temperature to gastric function [6], frequency of gastric myoelectrical activity [7], gastric emptying time, gastrin release, gastric acid secretion [8], esophageal cancer [9,10], and intraluminal upper gastrointestinal temperature and motility [5]. Although when it comes to energy metabolism, it has been assumed that higher dietary temperatures are dissipated during digestion and do not contribute to energy balance.

One of the most immediate responses of body cells to higher temperatures is the induction and increased synthesis of heat shock proteins (HSPs), especially HSP-70 [11,12] and HSP-90 [13,14]. HSP-70 [15] and HSP-90 [16] possess N-terminal adenosine triphosphatase fragments at their ends and tightly regulate adenosine triphosphate (ATP) activity and ATP hydrolysis [13,17-19], providing the heat energy to drive the adenosine diphosphate to ATP conversion. Indeed, cells exposed to higher temperatures increase HSP activity [11-14], and the time profile of peripheral blood mononuclear leukocytes HSP-70 response to in vitro heat shock is temperature dependent [11,20]. For instance, under in vitro hyperthermic conditions (40-41 °C), the time course was characterized by a sharp rise in HSP-70 concentration immediately after heat shock treatment (*P*<.05 for 40 °C at 0 hours), followed by a steady and progressive decline over time [11].

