There is ample literature on the effects of heat stress on fat deposition [35], insulin sensitivity [36], and the facilitating role of HSPs in adiposity [37-39]. The most direct evidence supporting our hypothesis comes from studies conducted on pigs. Exposure to low or high ambient temperatures directly impacts heat production and energy balance in pigs [40]. Heat stress causes enhanced adiposity [41] and growth performance through reduced energy and nitrogen use [42]. However, it is noteworthy that novel observations challenge this long-held traditional dogma, linking reduced productive output during heat stress to decreased nutrient intake. It is now clear that the heat stress response profoundly changes postabsorptive carbohydrate, lipid, and protein metabolism independently of decreased feed intake through harmonized alterations in fuel supply and use by various tissues [43]. One might argue whether heat stress in pigs is relevant to the effects of food temperature on energy metabolism in humans, especially when there is no direct evidence to show that ingesting hot food raises body temperature to such an extent. In addition, it may be argued that the association of HSPs with obesity does not automatically infer causation, and it is well known that these systems respond to metabolic stress. Therefore, to test this hypothesis, we prepared a short proposal to conduct a clinical trial, as described in the *Methods* section.

Altogether, these trials might provide preliminary evidence that HSPs contribute to obesity and weight regain. There is evidence that other HSPs, that is, HSP-A12A, regulate adipocyte differentiation and diet-induced obesity through positive feedback regulation with PPARγ (peroxisome proliferator-activated receptor gamma) [44].

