### Procedures

The day before the experimental session, the participants will be instructed to avoid alcohol, caffeine, and strenuous exercise and to drink plenty of water for 24 hours. On the day of the experimental session, the participants will be asked to arrive at the laboratory adequately rested and will be provided with boluses of soups (each 100 ml) with a predefined temperature to be taken once (to overcome the problem of temperature dissipation).

The energy content of bolus diets (including the thermoneutral diet and temperature-graded bolus diets) will be matched to each of the participant’s objectively calculated energy demands [62] and will be provided in the following manner: 20% energy for breakfast, 50% for lunch, and 30% for dinner. This procedure will facilitate the administration of boluses with graded temperatures (eg, +5 °C increments) with a fair precision from 37 °C to 52 °C, which is both ethical and within the optimal drinking temperature of 57.8 °C and <85 °C for the maximum temperature used to serve hot drinks such as coffee [63].

After assuring sufficient hydration (urine-specific gravity <1.025) [64], the participants will be instrumented in a thermoneutral room (approximately 25 °C) and then will be entered into a whole-body calorimeter regulated to 35 °C with approximately 20% relative humidity, where they will rest in an upright seated position for a 30-minute habituation period while steady-state measurements will be obtained.

The dietary temperature will be measured using a noncontact thermometer. All drinks and a standardized diet will be served at room temperature to maximize gastric emptying and fluid uptake while minimizing diuresis. It is expected that by using this metered intake to control for intake pacing, ingestion will be completed between 3 minutes and 5 minutes and will control for heat dissipation of foods and fluids as well. To avoid thermal injury while providing a satisfactory sensation to the participants, the optimum temperature for serving hot fluids and meals will be observed [63].

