The drinks and meals will be consumed at a speed that is as rapid as the participants can comfortably manage, which is described elsewhere in detail (mean 11 seconds for 200 mL and 38 seconds for 500 mL) [65,66]. The intraesophageal and intragastric temperatures will be monitored using thermocouples, which is a widely used technique [67]. As currently there is no specific dynamic model for real-time monitoring or measuring of temperature changes of digested meals or drinks along the alimentary tract, inner food and drink temperature will be estimated using the inverse heat conduction problem methodology on surface temperature measurements obtained using thermography [68]. For practical and physiological purposes, considering the applied speed of ingestion, the magnitude of temperature changes along the alimentary tract could be considered as negligible [65-67,69,70].

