### Measures

All outcome measures will be measured at 0, 6, and 12 weeks. The participants will be asked to follow their assigned diet served at 37 °C, 42 °C, 47 °C, and 52 °C for 12 weeks.

Blood samples will be collected from each participant for analysis after 12-hour fasting, 3 times during the study (at the beginning and 6 and 12 weeks later).

Adipose tissue biopsies, protein isolation, and in vitro cell culture experiments will be performed as described elsewhere [33].

Cellular HSP-70 and HSP-90 levels will be measured to determine the thermic response to feeding, that is, evaluation of the causal relationship among higher dietary temperature, HSP-70/HSP-90 concentrations, and their time profile, as well as measures of obesity, aerobic fitness, resting metabolic rate, and diet-induced thermogenesis.

Food diaries will be analyzed using software to determine energy intake and macronutrient content.

An automated respirometer system plus a whole-body direct calorimeter, as the gold standard, will be used to measure energy expenditure and substrate utilization, aerobic fitness, resting metabolic rate, diet-induced thermogenesis, and markers of protein and fat catabolism to evaluate whether dietary temperature influences metabolism and surrogate end points of obesity in participants, such as weight and waist-hip ratio.

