### Sample Size Calculation

As the choice of type I errors (α, false positive), type II errors (β, false negative), and effect size may be quite arbitrary [79], we suggest calculating the sample size or power using the *R* value (eHSP-70 to iHSP-70 ratio) for a pilot study (alternatively, owing to feasibility, a preliminary study may be conducted on mice or rats).

Furthermore, as providing a priori sample size calculation is misleading and the presentation of CIs—although serving the same purpose—is superior [80], it would be better to use the CI of the *R* value to calculate the sample size based on the feasibility of a priori assumptions about the study results and available resources. In addition, because foods and drinks may be served and consumed at even wider temperature ranges, it would be instrumental to calculate sample sizes based on wider *R* ranges (approximately 0.2-6).

According to Krause et al [30], assuming the ratio *R* = (eHSP-70) / (iHSP-70) = 1 for the controls (resting and unstimulated) and assuming a moderate-hot meal temperature may produce a shift in *R* to up to 5, which is paralleled by an increase in inflammatory markers and stimulation of cell proliferation, *R* values >5 can be considered as an exacerbated proinflammatory response. However, for a conservative calculation, we suggest using *R=*2*.* According to Hunter-Lavin et al [81], heat-shocked cells simultaneously measured HSP-70 at 37 °C (*R*=1.00), 39 °C (*R*=1.45), 42 °C (*R*=0.65), 43 °C (*R*=0.48), and 45 °C (*R*=1.97), this later temperature confirms a proinflammatory response.

Note that at 45 °C (*R*=1.97), there is a turning point compared with that at 43 °C. This means that if a study intends to investigate wider ranges of meal temperature, it is necessary to calculate an array of expected *R* values and then choose the maximum calculated sample size. For an *R* value between 0.22 and 1.1, a sample size of 9 participants is needed to achieve 80% power [1], whereas an *R* value between 1.8 and 6 would require 75 participants to achieve 90% power [2].

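### The plan calls temperature change along the gut negligible, against its own text, and carries cell-culture temperatures and R values over to meal temperature with no step linking the two.

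*Protocol article*

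**What the plan says.** **Temperature inside the body.** Procedures states that, given how fast the soup is swallowed, "the magnitude of temperature changes along the alimentary tract could be considered as negligible". The same section says "The intraesophageal and intragastric temperatures will be monitored using thermocouples" and plans to estimate inner food temperature by inverse heat conduction. The Background describes thermal exposure of the gastrointestinal tract as "being greatest at the mouth, followed by the esophagus and stomach, with the latter exposed for a greater time".

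**From cells to meals.** Under Weight Regain and HSPs, in vitro heat-stress temperatures of 37 to 41.5 °C are said to simulate, in theory, the response to hot meals and drinks. Sample Size Calculation reasons from "assuming a moderate-hot meal temperature may produce a shift in" R of up to 5, suggests R = 2 as the conservative value, and lists R from heat-shocked cells: 1.00 at 37 °C, 1.45 at 39 °C, 0.65 at 42 °C, 0.48 at 43 °C and 1.97 at 45 °C. It then uses this pattern to advise on studies of wider meal-temperature ranges. The same section ties R to peripheral blood mononuclear cells.

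**Exposure and outcome.** Measures gives an "assigned diet served at 37 °C, 42 °C, 47 °C, and 52 °C for 12 weeks", and Procedures gives "boluses of soups (each 100 ml) with a predefined temperature". Primary Subset B includes HSPs in plasma and total leukocytes, and anti-HSP antibodies. Blood is drawn after a 12-hour fast.

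**The concern.** Two links in the exposure chain are asserted rather than shown.

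The first runs from the served soup to the gut. If change along the tract is taken as negligible, the served temperature becomes the temperature at the gut wall. The plan's own anatomy and instruments imply otherwise.

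The second runs from the gut to the cells in which HSPs are read. Served soup at 42 °C and a cell held at 42 °C are different exposures, yet the R argument moves from one to the other.

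At stake is what the trial can say about its mechanism. A flat leukocyte HSP result could be taken to mean that heat of this degree does not induce HSPs, although those cells may hardly have warmed. A positive result could not be tied to a temperature that any tissue experienced. The R shift behind the sample-size reasoning would also rest on cell temperatures that the meals are not shown to produce.

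**Working it through.** **1. The passages side by side.**

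- The negligible-change sentence rests on speed of ingestion, with cited drinking speeds of "mean 11 seconds for 200 mL and 38 seconds for 500 mL". Speed can bear only on the swallow. The soup then stays in the stomach, which the Background says is exposed for longer than the mouth or oesophagus.
- The Background has exposure falling from mouth to stomach. The sentence has it essentially constant.
- The thermocouples would record the very change that the sentence sets aside.

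**2. How far could circulating cells warm?** The documents give no figure for body or blood warming, so there is nothing of theirs to reproduce. This calculation does not test the sentence about the gut lumen. It tests only the step from serving temperature to cell temperature.

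Inputs from the documents: serving temperatures 42, 47 and 52 °C against a 37 °C reference (Measures); 100 mL bolus; 500 mL, which appears only as a drinking-speed figure; BMI 25 to 35 kg/m².

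Assumptions not in the documents: soup behaves as water (4.18 kJ/kg/°C, 1 kg/L); mean body specific heat 3.47 kJ/kg/°C; body mass 60 to 110 kg, central value 80 kg; full mixing and no heat loss.

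Formula: rise = V × 4.18 × (T − 37) / (M × 3.47 + V × 4.18).

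For 500 mL at 52 °C, the excess heat is 0.5 × 4.18 × 15 = 31.35 kJ. At 80 kg the denominator is 277.6 + 2.09 = 279.69 kJ/°C, so the rise is 0.112 °C.

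| Soup | Body mass | Mean body rise |
|---|---|---|
| 500 mL, 52 °C | 60 kg | 31.35 / 210.29 = 0.149 °C |
| 500 mL, 52 °C | 80 kg | 0.112 °C |
| 500 mL, 52 °C | 110 kg | 31.35 / 383.79 = 0.082 °C |
| 500 mL, 47 °C | 80 kg | 20.9 / 279.69 = 0.075 °C |
| 500 mL, 42 °C | 80 kg | 10.45 / 279.69 = 0.037 °C |
| 100 mL, 52 °C | 80 kg | 6.27 / 278.02 = 0.023 °C |
| 1 L, 52 °C | 80 kg | 62.7 / 281.78 = 0.22 °C |

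**3. Volume needed to reach 39 °C,** the lowest heated-cell temperature with a quoted R. Soup that ends at 39 °C gives up 13 °C, so V = 2 × 277.6 / (4.18 × 13) = 555.2 / 54.34 = 10.2 L at 52 °C for 80 kg.

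**4. Sensitivity, 500 mL at 52 °C and 80 kg.**

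- Heat mixed into only half of body mass: 0.22 °C.
- Heat mixed into 30% of body mass: 0.37 °C.
- Extreme bound, all heat held in 5 L of blood (density 1.06 kg/L and specific heat 3.7 kJ/kg/°C assumed): 31.35 / (19.61 + 2.09) = 1.44 °C. This is still short of the 2 °C needed to reach 39 °C.

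**5. Arm temperatures.** Measures lists 47 and 52 °C where the allocation text in Sample Size Calculation lists 49 and 54 °C. At 54 °C, 500 mL gives 35.53 / 279.69 = 0.127 °C at 80 kg, so the conclusion is the same under either set.

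**The case against.** **The calculation does not bear on the quoted sentence.** That sentence concerns food in the lumen, not core temperature, and rests on sources not at hand. This stands. A small whole-body rise neither confirms nor refutes luminal cooling. The case against the sentence is the internal conflict alone. That conflict is softened because the Background describes ordinary eating, whereas the sentence is qualified by rapid swallowing and by practical purposes.

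**The trial randomises dietary temperature, so tissue temperature is not needed.** This also stands for the main comparison. A reader might infer that the trial cannot answer its question. The documents do not support that: an intention-to-treat comparison by arm estimates the effect of serving temperature whatever any tissue experienced.

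**The plan already admits the problem.** A reader might take "there is no direct evidence to show that ingesting hot food raises body temperature to such an extent" as a concession. In context it is an objection that the authors raise about the pig heat-stress evidence, and they offer the trial as the answer. The Conclusions section lists the precision of the estimated food temperature as a limitation. Neither place links serving temperature to cell temperature.

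**Leukocytes are not the only readout.** Correct. Plasma HSPs, antibodies and adipose biopsies are planned, and these need not depend on heating of circulating cells. Nor do the documents support saying that blood cells never meet such temperatures, since blood draining the stomach may briefly be warmer than the whole-body mean.

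**How thermocouple data are analysed belongs in a fuller document.** Accepted. The absence of an analysis is not the point here; the stated assumption and the stated extrapolation are.

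**Conclusion.** The point holds in two limited parts. First, the negligible-change statement is at odds with the Background and with the thermocouples planned beside it, and should be removed or narrowed. Second, the step from culture temperature to meal temperature has no stated support, although R refers to blood mononuclear cells and part of Subset B is read in leukocytes drawn after a 12-hour fast, by which time brief warming would be expected to have passed.

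Under the listed assumptions, mean body warming at 80 kg is about 0.02 °C for one 100 mL bolus at 52 °C. For 500 mL at 80 kg it is about 0.04 °C at 42 °C, 0.075 °C at 47 °C and 0.11 °C at 52 °C, with a range of 0.08 to 0.15 °C at 52 °C over 110 to 60 kg. Reaching 39 °C would take about 10 L at 52 °C. These are whole-body values after a single intake.

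The effect on the planned 80 participants cannot be sized, because the sample-size section states neither a standard deviation nor a test. This is a point the sponsor should address. It does not undermine the randomised comparison.

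**What to change.** 1. Delete the negligible-change sentence, or restrict it to the swallowing phase.
2. From the sessions in which thermocouples are used, summarise by arm the peak oesophageal and gastric temperature and the area above the pre-meal temperature. Present these as a check on delivered exposure. Relate HSP and R changes to them only as a supportive, non-randomised exposure-response analysis.
3. State in Sample Size Calculation that the culture R values refer to cell temperature and do not justify the R shift assumed for a given meal temperature.
4. State that a null leukocyte HSP result does not exclude an effect in gut tissue.
5. Reconcile the arm temperatures given in Measures and in Sample Size Calculation.

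The cost is wording plus one descriptive and one supportive analysis. There are two drawbacks: the assumed R shift will look less plausible, and the thermocouple data may cover only the experimental sessions rather than 12 weeks of meals, so they would describe delivered exposure only on those days.

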### Measures

All outcome measures will be measured at 0, 6, and 12 weeks. The participants will be asked to follow their assigned diet served at 37 °C, 42 °C, 47 °C, and 52 °C for 12 weeks.

Blood samples will be collected from each participant for analysis after 12-hour fasting, 3 times during the study (at the beginning and 6 and 12 weeks later).

Adipose tissue biopsies, protein isolation, and in vitro cell culture experiments will be performed as described elsewhere [33].

Cellular HSP-70 and HSP-90 levels will be measured to determine the thermic response to feeding, that is, evaluation of the causal relationship among higher dietary temperature, HSP-70/HSP-90 concentrations, and their time profile, as well as measures of obesity, aerobic fitness, resting metabolic rate, and diet-induced thermogenesis.

Food diaries will be analyzed using software to determine energy intake and macronutrient content.

An automated respirometer system plus a whole-body direct calorimeter, as the gold standard, will be used to measure energy expenditure and substrate utilization, aerobic fitness, resting metabolic rate, diet-induced thermogenesis, and markers of protein and fat catabolism to evaluate whether dietary temperature influences metabolism and surrogate end points of obesity in participants, such as weight and waist-hip ratio.

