### Proposed Outcome Measures

#### Primary Outcome Measures to Be Assessed

*Subset A* denotes the change in BMI, total body fat, body weight, percentage body fat, lean body mass, percentage lean body mass, waist circumference, and waist-hip ratio from baseline to 12 weeks (time frame: 0, 6, 12, and n weeks). The measurements will be performed with light clothing before breakfast and preferably after voiding.

*Subset B* denotes changes in HSP-27, HSP-65, HSP-70, HSP-72, and HSP-90 (in plasma and total leukocytes) and anti–HSP-27, anti-HSP-65, anti-HSP-70, anti-HSP-72, and anti-HSP-90 antibodies from baseline to 12 weeks (or whatever time is feasible, time frame: 0, 6, 12, and n weeks).

*Subset C* denotes changes in motilin, fasting glucose, insulin, C-peptide, 2-hour glucose, and insulin plus homeostasis model assessment–estimated insulin resistance from baseline to 12 weeks (or whatever time is feasible, time frame: 0, 6, 12, and n weeks).

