Changes in the calculation of the *R* value are suggested to be valid during heat exposure, as *R* values are associated with the heat exposure of peripheral blood mononuclear cells to different temperatures within a physiological range [30]. Precautions that should be considered could include, but are not limited to, correction for noncompliance of the participants, adjustment for multiple comparisons, and innovative study design.

A total of 80 patients will be randomized equally (1:1:1:1) between the 3 active treatments and the thermoneutral group. Overall, 20 participants will be randomly allocated to the thermoneutral diet group (37 °C): 20 at 42 °C, 20 at 49 °C, and 20 at 54 °C. The primary analysis will be intention-to-treat for the whole study cohort.

It is possible that there are multiple roles of HSPs in body weight, weight regain, and composition, probably related to the exposure time during diet ingestion (and also dietary temperature acclimatization during short-term periods, midterm periods, and long-term periods and presence or absence as well as the degree of insulin resistance in people). Thus, conducting a clinical trial for 12 weeks would provide a sufficient time course to investigate this point.

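### All scheduled blood draws are fasting, so the HSP data can show a 12-week change in resting levels but not the response to feeding or the meal-induced R behind the sample size

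*Protocol article*

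**What the plan says.** All references are to the Protocol article.

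- **Schedule (Measures).** "All outcome measures will be measured at 0, 6, and 12 weeks". For blood, "Blood samples will be collected from each participant for analysis after 12-hour fasting, 3 times during the study".
- **Aim (Measures).** "Cellular HSP-70 and HSP-90 levels will be measured to determine the thermic response to feeding". The sentence explains this as evaluating the causal relationship among "higher dietary temperature, HSP-70/HSP-90 concentrations, and their time profile", together with obesity and metabolic measures.
- **Primary outcome (Primary Outcome Measures, Subset B).** Changes in five HSPs, "in plasma and total leukocytes", and in five anti-HSP antibodies, from baseline to 12 weeks.
- **Sample size (Sample Size Calculation).** R is set to 1 for controls at rest without stimulation. A moderately hot meal is assumed to move it to as much as 5, and R = 2 is suggested as conservative. Changes in the calculated R "value are suggested to be valid during heat exposure".
- **Kinetics (Background).** In vitro, HSP-70 rises sharply as soon as heating ends, "followed by a steady and progressive decline over time".

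**The concern.** The plan names an HSP response to feeding and builds its sample-size argument on a ratio shifted by a hot meal. Every scheduled blood draw, however, comes after a 12-hour fast. The article's own in vitro description has HSP-70 highest straight after heating and falling from then on. A person fasted for 12 hours may be close to the resting, unstimulated state to which the article gives R = 1.

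HSP induction is the central hypothesis, and Statistical Analyses plans a mediation analysis of weight change through HSP levels. If the fasting data show no difference between arms, they cannot separate a meal that induced no acute response from one whose response had faded before the draw. The sample size would also refer to one measurement condition and the data to another.

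**Working it through.** **1. Stated use against scheduled samples**

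| Use of HSP data | Condition it needs | Scheduled blood that supplies it |
|---|---|---|
| Subset B, change over 12 weeks | Comparable samples at 0, 6 and 12 weeks | Yes, all three fasting draws |
| Response to feeding (Measures) | Sample during or after a meal | None |
| Meal-induced R (Sample Size Calculation) | Sample during or soon after heat exposure | None |

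None of the three draws falls within 12 hours of a meal. The baseline draw precedes the assigned diet, so two draws are informative about treatment, and both are fasting. The 2-hour glucose in Subset C implies a later, non-fasting draw, but no HSP is assigned to it. Measures gives no timing of biopsies relative to meals. The crossover section places biopsies and plasma only before and after the dietary treatment.

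**2. The plan's own figures**

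Sample Size Calculation gives 9 participants for 80% power (R 0.22 to 1.1) and 75 for 90% power (R 1.8 to 6). No SD of R, alpha, sidedness, test or contrast is stated, so neither figure can be reproduced. They can only be inverted for the SD they would imply:

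SD = δ × √(n/k) / (z for alpha + z for power), with k = 2 for two arms of n each and k = 1 for one sample or pairs.

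- n = 75, 90% power, δ = 1 (R = 2 against 1), 75 per arm, two-sided 0.05: SD = √37.5 / (1.960 + 1.282) = 6.124 / 3.242 = 1.89. Reading 75 as one sample, per arm, two-arm total or four-arm total, one- or two-sided, gives 0.94 to 2.96.
- n = 9, 80% power, δ = 1.1 − 0.22 = 0.88, same set of readings: SD from 0.33 to 1.06.

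Nothing in the article confirms or refutes any of these.

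**3. How much of an acute rise would remain (assumption)**

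The article gives no in vivo half-life h. Assume exponential decline and a last hot meal exactly 12 hours before the draw:

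- remaining fraction f = 2^(−12/h)
- multiplier on n for the same power at equal SD = 1/f²

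For power, assume further an R shift of 1 at exposure, SD of R = 1, two-sided 0.05 and 20 per arm. Then power = Φ(f × 1/√(2/20) − 1.960) = Φ(3.162f − 1.960), counting rejection in the expected direction only. At exposure f = 1, and power = Φ(1.202) = 88.5%.

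| Assumed h (hours) | f | 1/f² | Power, SD = 1 |
|---|---|---|---|
| 2 | 0.016 | 4096 | 2.8% |
| 4 | 0.125 | 64 | 5.9% |
| 6 | 0.25 | 16 | 12% |
| 12 | 0.50 | 4 | 35% |
| 24 | 0.71 | 2 | 61% |

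The answer also depends on the assumed SD. With SD = 0.5, power at 12 hours is 88.5% for h = 12 and 99.4% for h = 24. With SD = 1.5, it is only 55.9% even at exposure. This model covers the acute component alone; any sustained effect of 12 weeks of hot meals is left out.

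**The case against.** The strongest reply is that Subset B never promises an acute measurement. It is worded as a change from baseline to 12 weeks, half its analytes are antibodies, and the Thermic Response section cites HSP-70 increases that depend on the number of heat-acclimation days. Fasting draws suit that outcome. This stands. A reader might infer that the HSP outcome is unusable or that a null result would mean nothing. The document does not support that: a null would mean that no sustained shift in fasting HSPs was detected.

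Three further points also stand:

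- The time profile may mean weeks 0, 6 and 12. Sample Size Calculation speaks of acclimatization over short, middle and long periods and calls 12 weeks a sufficient time course. The schedule would then fit that phrase.
- The fasting rule is stated for blood. The sentence on cellular HSPs follows the one on biopsies, whose procedures are left to a cited source, so one cannot say that every HSP measurement is fasting.
- The Background kinetics are in vitro, and the statement on R rests on heated mononuclear cells. Neither is a sampling rule for participants.

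A reader might also infer a 16-fold to 4096-fold loss in sample size. Those values come from assumed half-lives of 2 to 6 hours; 12 and 24 hours give 4-fold and 2-fold, and the article supports none of these in particular.

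The reply does not remove the phrase on response to feeding, which fasting blood cannot meet on any reading of the time profile. Nor does it remove the difference between a meal-induced R and a fasting R. These are conflicts between stated items, so a fuller protocol would not resolve them by adding detail.

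**Conclusion.** The point holds in limited form. As written, the blood schedule supports a 12-week change in resting HSPs and nothing acute. It cannot deliver the response to feeding named in Measures, and the R behind the sample size belongs to a different measurement condition from the samples to be collected.

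The conflict rests on the text alone. How much signal would be lost is unknown: about 2% to 71% of an acute rise would remain under half-lives of 2 to 24 hours, all assumed. The power figures further assume an R shift of 1, an SD of 1 and a two-sided 0.05 test. They illustrate direction and do not estimate this trial's power. The figures of 9 and 75 participants are not shown to be wrong; they cannot be checked.

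**What to change.** Choose one of two routes. The Results section says the trial has not been initiated, so both are open.

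**(a) Limit the claims to what is sampled.** Define the HSP part of Subset B, and the HSP mediator in the mediation analysis, as change in fasting levels. Remove the response-to-feeding statement from Measures, and say that the time profile means weeks 0, 6 and 12. Stop using the heat-exposure R to justify 80 participants; any R-based calculation should use a fasting R with its SD. The cost is wording, plus a less favourable sample-size claim.

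**(b) Add timed samples.** Keep the fasting draws for Subset B. In the laboratory session already planned, also assay HSP-70 and R in blood taken before the temperature-graded bolus and at set times after it. Compare each arm with the 37 °C arm under the same ambient conditions. That comparison is needed because Procedures puts participants in a calorimeter at 35 °C, so a rise within one arm would mix ambient with dietary heat. Use only these samples for the response-to-feeding and R claims. The cost is a few extra tubes and assays per session. A single post-meal tube would not give a within-day time profile.

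Under either route, state the timing of biopsies relative to meals.
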